### Ethical considerations

The study protocol and procedures have been reviewed and approved by the Helsinki committees (institutional review board) at both of the study sites, and by Abt Associates (the coordinating institution on which US CDC relies). In addition, extraction of data from the CHS EMR was approved by the Data Use Committee of the Clalit Research Institute.

All participants complete written informed consent in Hebrew. Small gifts (such as a gift card) are given to participants at study milestones like completion of enrollment, blood draws, and completion of end-of-season survey. Influenza test results are given to those participants who ask to receive them. Given the research nature of the laboratory methods and time delays in batch testing, mqRT-PCR findings are not available to inform clinical decisions.

## Discussion

We described the recruitment, enrollment, active surveillance, data collection, laboratory methods, and data management procedures for the SHIRI cohort – a US CDC-sponsored prospective study, overseen by CHS, of approximately 2300 HCP at two hospitals in Israel. In this study, we will describe the frequency of influenza virus infections among HCP in Israel. Using a broad case definition of respiratory illness, we aim to identify a wide range of ARFI in order to assess more accurately the burden of respiratory illness among HCP. Due to CHS’s extensive EMR, we will have the ability to look at HCP influenza vaccination records up to 10 years prior to study enrollment in order to better understand how HI antibody titers differ depending on the number and specific combinations of prior influenza vaccinations. We will also be able to evaluate influenza vaccine effectiveness in preventing medically attended and non-medically attended influenza illness and associated missed work days.

The findings from the SHIRI cohort will increase our understanding of the burden of acute respiratory illnesses, and influenza virus illness specifically, among HCP in Israel. The unique design of the study, which includes comprehensive medical and vaccination data, active surveillance using a broad case definition, and both molecular and serologic diagnostics, will provide important data on influenza vaccine immunogenicity and effectiveness among HCP. The combination of insights about influenza burden and vaccine effectiveness may potentially inform influenza vaccine policy for HCP in Israel and internationally.

### Strengths

Our study benefits from the fact that all enrolled HCP are members of CHS, and therefore extensive information is recorded in the EMR, which provides real-time data about ambulatory visits, hospitalizations, and medication use. In addition, the EMR provides reliable historic data about the participants, such as prior vaccination information, socio-economic variables, and data about health status and health behaviors. In our study, even if an ARFI is not reported through the SMS surveillance system, daily monitoring of the EMR for medical visits and medications will allow us to identify illnesses and contact participants directly in order to collect respiratory specimens and complete the illness survey. Combining our study with EMR data and data from the two hospitals’ human resources departments will also allow us to reliably map the impact of illness on missed work and to evaluate days worked when ill (presenteeism).

In addition, the broad case definition of an ARFI promises to be more sensitive for influenza illness than case definitions used in previous HCP research [24] and should allow us to characterize a continuum of mild to moderately severe illnesses. Another strength is that the two study sites (Soroka University Medical Center and Beilinson Hospital) are among the largest hospitals in Israel, and the populations they serve and the HCP they employ vary in socio-demographic and economic characteristics. Soroka University Medical Center, the only general hospital in the Negev region in southern Israel, serves two main local populations: Jews, who mostly live in urban settings, and Bedouin Arabs, who live in a range of settlement types, from cities to unrecognized rural villages that lack electricity and running water [42, 43]. Beilinson Hospital, located in central Israel, serves a mostly urban population of a relatively higher socio-economic status compared to Soroka University Medical Center. Conducting our study in these two different settings may allow us to identify socio-demographic differences in KAP, vaccine uptake, and influenza illness attack rates. The use of mixed methods, including laboratory, clinical and epidemiological quantitative data, and in-depth qualitative interviews, creates a comprehensive approach, which is particularly important when trying to understand issues of influenza vaccine compliance and hesitancy. Finally, the study cohort includes several unique sub-studies.

### Limitations

Our study has at least four limitations. First, our ability to generalize vaccine effectiveness findings from the study years to the potential preventive value of an influenza vaccine program may be limited. The effectiveness of the vaccine depends in part on the types of viruses circulating and the antigenic and genetic match between vaccine components and circulating strains in a given year. The precision of the estimates will also depend on the number of influenza cases.

Second, we will be cautious in interpreting self-reported information, given potential biases in recall and self-presentation. While some of the information collected through active surveillance can be verified with administrative data, other information, such as symptoms for non-medically attended illnesses, cannot be verified by another data source.

Third, although the random stratified sampling design intentionally includes HCP with a mixture of characteristics and work responsibilities, there are relatively few HCP in some of the strata. For example, few male medical assistants and support personnel are employed at the two hospitals, and therefore it is unlikely that we will be able to enroll large numbers from this category. This may limit our ability to examine the association between the frequency of influenza illness and specific combinations of age, sex, and occupation.

Fourth, during the third wave of recruitment we accept volunteers, regardless of age, profession, or vaccine status, which can present a sampling bias. However, characteristics of these volunteer participants will be compared with those of participants recruited during the first two waves in order to evaluate potential differences between the groups.

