#### Recruitment

In order to recruit HCP with diverse socio-demographic characteristics, occupational responsibilities, and influenza vaccination histories, eligible HCP were invited to participate using a stratified sampling strategy that targeted eligible participants in groups (strata) categorized by sex, age, occupation, and previous year influenza vaccination status. This systematic approach was intended to minimize convenience sampling, which can introduce both known and unknown biases. Each group includes individuals with unique characteristics known to potentially affect influenza vaccine immunogenicity and effectiveness.

At CHS, a list of eligible HCP at each facility was generated and categorized into groups based on age (18–34, 35–49, ≥50 years old), sex, occupational categories (1- Physicians; 2 - Nurses, medical therapists, and professional technicians; and 3 - Medical assistants and support staff), and prior season influenza vaccination status (yes vs. no). Thus, prior to each year of the study, the sample is drawn from 36 unique strata (2 sexes * 3 age groups * 3 occupation groups * 2 prior season vaccination status groups). This stratified sampling strategy will be applied to potential new participants each year.

At each hospital, goals are set for the minimum and maximum number of enrollees per strata; then, recruitment is implemented in three waves. During the first wave of recruitment, HCP from the 36 strata are invited at random to participate in the study. Next, in Wave 2, we identify study strata where additional recruitment is needed and expand direct invitations to additional HCP who have not yet been invited to join the study. In strata where all HCP have been contacted but recruitment goals have not been met, we will recruit similar HCP, prioritizing HCP who are similar in previous vaccination status, followed by age, sex, and lastly by profession. Finally, in Wave 3, we accept volunteers to meet the total sample goals for each facility. All potential enrollees will be recorded in a recruitment log in order to track invitations, acceptance, and refusal and reasons for refusal.

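### The article concedes that Wave 3 volunteers may bias the sample, but the only check it names compares their characteristics, which cannot show whether attack rate or VE differs by wave

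*Protocol article*

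**What the plan says.** Under Recruitment, the article states that "the sample is drawn from 36 unique strata", formed from sex, age group, occupation group and prior-season vaccination. At each hospital "goals are set for the minimum and maximum number of enrollees per strata". The reason given is that "This systematic approach was intended to minimize convenience sampling, which can introduce both known and unknown biases". Wave 1 invites HCP at random within strata. Wave 2 fills shortfalls and, where a stratum is exhausted, substitutes similar HCP, matching on vaccination history first. Finally, "in Wave 3, we accept volunteers to meet the total sample goals for each facility". The section adds that "All potential enrollees will be recorded in a recruitment log".

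Limitations says of the same wave that "during the third wave of recruitment we accept volunteers, regardless of age, profession, or vaccine status", and concedes that this may bias the sample. The response offered is that "characteristics of these volunteer participants will be compared with those of participants recruited during the first two waves".

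Two other places matter. Eligibility criteria foresees that some entry restrictions may be dropped if enrollment falls short, and says that outcomes may then be compared across the relaxed criteria. Data analysis of VE adjusts for study year, calendar time and a vaccination propensity score, and adds any other confounder that shifts the VE estimate by more than 5%. It names study site as one candidate for that screen but does not mention recruitment wave.

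**The concern.** The stratified scheme exists to keep convenience sampling out, and Wave 3 lets some of it back in. The article says so openly, but the check it names answers a different question from the one the concession raises. Two groups can look alike on recorded characteristics and still differ in their risk of influenza or in their readiness to report illness and take a swab. Cases are found through participants' own reports and mostly self-collected swabs, so readiness to report feeds directly into the case count. A comparison of characteristics says nothing directly about the two quantities that the study will publish from these cases: influenza illness rate (first objective) and VE (fourth objective).

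There is also a gap in the recruitment rule. Per-stratum maximums are set, yet the only limit named for Wave 3 is the facility total. A reader cannot tell whether a stratum already at its maximum may go on growing.

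**Working it through.** **1. Strata.** 2 sexes x 3 age groups x 3 occupation groups x 2 vaccination histories = 36, which reproduces the article's count. Limitations sets aside three of these four stratifiers for volunteers; sex is not named.

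**2. The two relaxations side by side.** Dropping an entry restriction and admitting volunteers are both ways of reaching the enrollment target.

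| Relaxation | Where | Check named |
|---|---|---|
| Entry restrictions dropped | Eligibility criteria | Outcomes may be compared across the relaxed criteria |
| Volunteers admitted (Wave 3) | Limitations | Characteristics compared with Waves 1-2 |

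The second check is the weaker one, although it is attached to the relaxation for which the article itself concedes bias.

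**3. What a difference by wave could do.** The article gives no number, coverage or risk for Wave 3, so this is an illustration.

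- From Cohort size: attack rate 10% (read as overall), coverage 40%, true VE 50%.
- Implied rates in Waves 1-2: unvaccinated 0.10 / (1 - 0.4 x 0.5) = 0.125; vaccinated 0.0625.
- Assumed: volunteer share f = 0.1 to 0.3; volunteer coverage c = 0.4 to 0.8; risk ratio r = 0.7 to 1.5 against Waves 1-2, the same in vaccinated and unvaccinated. True VE is therefore 50% in both groups.

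Pooled unvaccinated rate = 0.125 x [0.6(1-f) + f(1-c)r] / [0.6(1-f) + f(1-c)].
Pooled vaccinated rate = 0.0625 x [0.4(1-f) + fcr] / [0.4(1-f) + fc].

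- f = 0.3, c = 0.8, r = 1.5: unvaccinated 0.125 x 0.51/0.48 = 0.1328; vaccinated 0.0625 x 0.64/0.52 = 0.0769; crude VE = 1 - 0.0769/0.1328 = 42.1%.
- f = 0.3, c = 0.8, r = 0.7: unvaccinated 0.125 x 0.462/0.48 = 0.1203; vaccinated 0.0625 x 0.448/0.52 = 0.0538; crude VE = 55.2%; attack rate 0.125 x 0.462 + 0.0625 x 0.448 = 8.6%.
- c = 0.4 (same coverage as the rest), f = 0.3: crude VE stays at 50%, but the attack rate is 0.10 x (0.7 + 0.3r), that is 9.1% at r = 0.7 and 11.5% at r = 1.5.

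Over the grid, crude VE runs from 42% to 55% and attack rate from 8.6% to 11.5%. Since VE was set equal in both groups, stratifying or adjusting for wave returns 50%.

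**4. What an analysis without Wave 3 can show.** With the 2340 participants of Cohort size and the rates above, expected events are 2340 x 0.6 x 0.125 = 175.5 unvaccinated and 2340 x 0.4 x 0.0625 = 58.5 vaccinated. The SE of the log rate ratio is sqrt(1/175.5 + 1/58.5) = 0.151, and the 95% CI for a VE of 50% is about 33% to 63%. Losing 10% of events at random gives SE 0.151/sqrt(0.9) = 0.159 and a CI of 32% to 63%; losing 30% gives 0.151/sqrt(0.7) = 0.180 and 29% to 65%.

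Now take the 42.1% case. Expected events are 149.2 unvaccinated and 93.6 vaccinated with Wave 3, and 122.85 and 40.95 without it. The two estimates differ by ln(0.579/0.5) = 0.147 on the log scale. The SE of that difference is sqrt[(1/122.85 - 1/149.2) + (1/40.95 - 1/93.6)] = 0.123. The largest downward shift in the grid is therefore only about 1.2 standard errors.

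**The case against.** The strongest reply is that the authors disclose this limitation themselves, and that an analysis by wave belongs in an analysis plan that is not shown. Disclosure is to their credit, and absence of the analysis alone would be no finding. What stands is narrower: the article does choose a check for this bias, and the one it chooses does not look at outcomes.

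Other points against it carry weight:

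- The comparison of characteristics is not empty. The study holds vaccination and medical-visit history, health status and attitudes to illness and vaccination, which are proxies for risk and health-seeking.
- VE is an internal contrast, and the propensity score gives some protection. The list of further confounders is open, so wave could be examined. With r common to vaccinated and unvaccinated, crude VE moves only if volunteers differ in both coverage and risk.
- Under-reporting is countered by telephone and in-person follow-up (Active surveillance) and by monitoring of medical records (Strengths).
- Sample size for incidence calculations describes incidence as applying to the sample studied, so the attack-rate concern is mainly about generalizing. The Discussion nevertheless speaks of influenza frequency in HCP in Israel.
- Waves 1 and 2 contain only those who accepted an invitation, so leaving out Wave 3 does not remove self-selection.

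A reader might infer three stronger things that the documents do not support. First, that Wave 3 overrides the stratum maximums: neither section says they are lifted. Second, that the study will declare volunteers unbiased if characteristics match: Limitations promises only to look for differences between the groups. Third, that VE would be inflated. If vaccinated volunteers alone had half the risk and made up 10%, 20% or 30% of the vaccinated, VE would read 52.5%, 55% or 57.5% (for 10%: 1 - [0.9 x 0.5 + 0.1 x 0.25] = 0.525). That scenario builds in a VE of 75% among volunteers, and nothing in the documents supports it.

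**Conclusion.** The point holds as a cheap improvement to the analysis. A sampling bias is conceded, and the one check tied to it can partly flag the problem but cannot show whether attack rate or VE differs. The article already allows an outcome comparison for a parallel relaxation. Whether the stratum maximums bind in Wave 3 is unclear and should be stated.

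The size and direction of any bias cannot be computed from the documents. The ranges of 42% to 55% for crude VE and 8.6% to 11.5% for attack rate rest wholly on the assumed share, coverage and risk of volunteers, and they are before the planned adjustment. They show that either direction is possible, and that the attack rate can move even when VE does not.

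**What to change.** 1. Keep recruitment wave as an analysis variable. The comparison already promised in Limitations requires it to be known, so no new data are needed.
2. Include wave among the candidates examined in the confounder screen of Data analysis of VE.
3. Report influenza illness rate and adjusted VE by wave, or with and without Wave 3, as a sensitivity analysis with intervals, beside the characteristics comparison.
4. Do not read a non-significant difference as proof of no bias; a comparison about 1.2 standard errors wide would often miss the shift shown above.
5. State under Recruitment whether the per-stratum maximums apply in Wave 3.

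The cost is one extra analysis and a wider interval in the version without Wave 3: about 29% to 65% instead of 33% to 63% if 30% of events were lost at random, on the Cohort size inputs.

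Capping Wave 3 by stratum is not part of this recommendation. It would work against the purpose of reaching facility totals and could not apply to the 596 HCP already enrolled in Year 1, so it is a trade-off for the steering committee.

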## Abbreviations

ARFI: Acute respiratory illness or febrile illness
CHS: Clalit Health Services
CVL: Clinical Virology Laboratory
EMR: Electronic medical record
GMT: Geometric mean titer
GMR: Geometric mean ratios
HCP: Healthcare personnel
HI: Hemagglutination inhibition
hMPV: Human metapneumovirus
ICD-9: The international classification of diseases, ninth revision
ICPC: International Classification of Primary Care Coding
IVE: Influenza vaccine effectiveness
KAP: Knowledge, attitudes, and practices
mqRT-PCR: Multiplex quantitative real-time reverse transcription polymerase chain reaction
PBMC: Peripheral blood mononuclear cells
RBC: Red blood cells
REDCap: Research Electronic Data Capture
RSV: Respiratory syncytial virus
SHIRI: Study of Healthcare Personnel with Influenza and other Respiratory Viruses in Israel
SMS: Short message service
US CDC: United States Centers for Disease Control and Prevention
